### Sample size calculation

7.4

To calculate a sufficient sample size for the primary analysis we choose the formula presented by Kuen Cheung et al. [20]. We set the target toxicity level to 0.10, an accuracy of 0.6 and an odds ratio to 2, as this is a fragile population. Therefore the project will include 40 patients unless the maximum tolerable dose meets the pre-specified stopping rules.

### Reporting and interpretation of statistical measures

7.5

The adaptive dose-finding trial will use probabilistic methods. Therefore, 95 % credibility intervals will be reported in relation to the MTD and the prevalence of the given dose. In the secondary analysis, a p-value below 0.05 will be considered statistically significant, and 95 % confidence intervals will be reported together with their corresponding effect size. All p-values will be two-sided, and no adjustment for multiple testing will be utilized (as these analyses are not the primary analyses). All results will follow the Extended CONSORT guidelines for dose-finding studies if they are available [21].

### Missing data

7.6

No missing data in relation to the primary analysis is expected as all measures are measured by healthcare professionals, therefore if data is missing it is assumed to be missing completely at random unless Little's test is statistically significant and no type I error seems to be present [22].

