### Exposure

6.4

The exposure is a categorical variable where the groups are defined as:•0.10 mg/kg methadone at the beginning of surgery.•0.15 mg/kg methadone at the beginning of surgery.•0.20 mg/kg methadone at the beginning of surgery.

When patients are included from the ED the orthopaedic doctor will contact the primary investigator [name], who will assign each patient to a methadone group (0,10 mg/kg, 0,15 mg/kg or 0,20 mg/kg) using the model-based Continual Reassessment Method (CRM). This method uses registered primary outcome from the previous included patients or the prespecified prior if no data has been collected (see Fig. 1). The assigned methadone group is registered into REDcap and will be used to estimate the individual dose of methadone, which is calculated by multiplying methadone group with patient weight. This individual methadone dose will be written on a case report file (CRF). The primary care provider from the ED is responsible for withdrawing study medicine and placing the syringe near the patient together with the CRF. The individual dose of methadone is administered intravenously by the certified registered nurse anaesthetist when anaesthesia is commenced. The CRF will follow the patient to the orthopaedic ward.

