### Primary analysis and treatment assignment

7.2

This trial uses the Bayesian continual reassessment method, therefore stopping guidelines and probabilistic priors in relation to toxicity MTD (maximal tolerable dose) need to be determined before inclusion of the first patient. The stopping rules for the trial include:•If 40 persons are included.•If the probability of the lowest dose exceeding a predetermined toxicity threshold (set at 0.10) is greater than 95 % and more than 10 persons are included.•If the 95 % credibility interval of the toxicity level for the MTD is between 0 and 0.10 (a clinically acceptable toxicity level) and more than 10 persons are included.•If all the above stopping rules are fulfilled and 10 participants are included.

The predetermined toxicity threshold for the lowest dose considers the assumption that toxicity increases with higher doses. Thus, if the toxicity at the lowest dose surpasses the clinically acceptable level of 0.10, further dose escalation should be avoided. The pre-specified prior to this analysis consists only of presumed toxicity levels of the different doses and the alpha parameter. The presumed toxicity levels for the three doses is set to 0.05, 0.1, and 0.2 for 0.10 mg/kg, 0.15 mg/kg, and 0.2 mg/kg, respectively, and alpha follows a *γ*(1*,* 1) distribution. After the specification of the prior and stopping rules, the method uses the dose-response curve to escalate or deescalate the doses in a non-conservative manner (see Fig. 2) and close arms if one or more stopping rules are met. The 1-parameter model estimates the MTD more efficiently by escalating through the doses faster [16]. This is acceptable because the risk of adverse events by respiratory depression is low. Furthermore, there may be difficulties fitting the model or obtaining consistent estimates of model parameters in a two-parameter model [16]. Thus, we choose to use the 1-parameter model for this study.

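### Missing toxicity outcomes are treated as missing completely at random by default, guarded only by a test that cannot see missingness caused by toxicity

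*SAP article*

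**What the plan says.** Section 7.6 (Missing data) starts from an expectation: "No missing data in relation to the primary analysis is expected as all measures are measured by healthcare professionals". It then gives a rule for the case where this fails: "if data is missing it is assumed to be missing completely at random unless" a two-part condition is met. With that condition, missing data are "assumed to be missing completely at random unless Little's test is statistically significant and no type I error seems to be present". It does not say how a patient without an outcome enters the model (omitted, imputed, or classified from other readings), nor what is done if the assumption is rejected.

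Section 6.2 (Primary outcome) has respiratory depression recorded on arrival at the orthopaedic ward and at 6 and 24 hours after surgery. Section 6.3 has staff of the orthopaedic department take the measurements. Section 6.4 (Exposure) says of the continual reassessment method (CRM): "This method uses registered primary outcome from the previous included patients". A missing outcome therefore matters during the trial as well as at the final analysis.

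**The concern.** The reason given for expecting complete data, that health professionals take the measurements, bears on how often readings are missing, not on why. In this trial the reason may be the outcome itself. Readings are tied to the orthopaedic ward, so a patient held elsewhere because of poor breathing could miss them. That is missingness depending on the unseen value, and treating it as ignorable understates toxicity.

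The safeguard does not address this. Little's test compares the observed variables of patients with and without the outcome. It can respond to toxicity-driven missingness only through observed variables that correlate with toxicity. Whether a particular significant result is a type I error cannot be read from the data, so even a significant test may be set aside by judgement.

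At stake are the next patient's dose and the final maximum tolerable dose (MTD), which section 8 says will be used in a future randomised trial.

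**Working it through.** **Inputs from the SAP.** Section 7.4: "We set the target toxicity level to 0.10, an accuracy of 0.6 and an odds ratio to 2", and "the project will include 40 patients unless the maximum tolerable dose meets the pre-specified stopping rules". Section 7.2: presumed toxicities "set to 0.05, 0.1, and 0.2 for 0.10 mg/kg, 0.15 mg/kg, and 0.2 mg/kg, respectively"; the prior "consists only of presumed toxicity levels of the different doses and the alpha parameter", with alpha following a Gamma(1,1) distribution; a one-parameter model.

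**Assumptions.** Power model, since section 7.2 says only one-parameter: p_d = s_d^α with s = (0.05, 0.10, 0.20). Chosen dose = the one whose estimate is closest to 0.10. The SAP does not say whether that estimate is plug-in or posterior mean, so both are shown. Missing rates are assumed, because the SAP gives none. Little's test is taken at 0.05, a level the SAP states only for secondary analyses.

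**Step 1: the plan's own figure.** The sample-size formula is not printed, so 40 was checked by simulation (neighbouring doses an odds ratio of 2 apart, MTD at each dose in turn, no early stopping). With complete data and N = 40, average correct selection is 0.64 for the CRM and 0.66 for the non-parametric benchmark. The stated accuracy of 0.6 is met, so the sample size is not the problem.

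**Step 2: effect of one lost toxicity.** With n_d patients and t_d toxicities at dose d, the posterior is proportional to

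e^(−α) × Π_d (s_d^α)^(t_d) × (1 − s_d^α)^(n_d − t_d).

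Plug-in is s_d^E(α); posterior mean is E(s_d^α). Estimates are listed for 0.10 / 0.15 / 0.20 mg/kg.

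| Data | E(α) | Plug-in | Choice | Posterior mean | Choice |
|---|---|---|---|---|---|
| 3/20 at 0.15 | 0.851 | 0.078 / 0.141 / 0.254 | 0.10 | 0.097 / 0.160 / 0.271 | 0.10 |
| 2/19 at 0.15 | 1.009 | 0.049 / 0.098 / 0.197 | 0.15 | 0.067 / 0.119 / 0.218 | 0.15 |
| 1/18 at 0.15 | 1.289 | 0.021 / 0.051 / 0.126 | 0.20 | 0.037 / 0.074 / 0.152 | 0.15 |
| 1/10 at 0.10 | 0.839 | 0.081 / 0.145 / 0.259 | 0.10 | 0.118 / 0.183 / 0.293 | 0.10 |
| 0/9 at 0.10 | 1.807 | 0.004 / 0.016 / 0.055 | 0.20 | 0.032 / 0.060 / 0.118 | 0.20 |

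Omitting one toxic patient moves the choice from 0.10 to 0.15 (rows 1 to 2) and from the lowest dose to the highest (rows 4 to 5), under both estimates. Losing a second toxicity (row 3) moves the choice to 0.20 under plug-in only.

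**Step 3: what Little's test would show.** Simulated with N = 40, the primary outcome incomplete, and dose plus none to five complete covariates unrelated to toxicity (4,000 runs per setting). Rejection rates are among trials with missing data.

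| Missing if toxic / non-toxic | Patients missing | Rejects |
|---|---|---|
| 5% / 5% (truly at random) | about 2 | 3–4% |
| 25% / 2% | about 2–3 | 3–5% |
| 50% / 2% | about 3–4.5 | 4–10% |
| 80% / 2% | about 4–7 | 4–16% |

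In the plausible settings (25% and 50%) power is close to the false-positive rate.

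**Step 4: effect over a whole trial.** The CRM was rerun with outcome-dependent missingness (3,000 runs per setting).

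- Lowest dose is the true MTD, 25% / 2% missing (about 2 of 40 patients): a dose above the MTD is selected in 37% of trials if missing patients are omitted, against 20% with complete data and 13% if missing is counted as toxic.
- Same, with 50% of toxic outcomes missing: 66% (omitted) against 11% (counted as toxic).
- Highest dose is the true MTD, 25% / 2% missing: counting missing as toxic selects that dose in 40% of trials, against 59% with complete data.

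**The case against.** **The SAP never says patients are dropped.** A reader might infer that it orders their removal from the model. It does not; section 7.6 states no mechanics, and a fuller plan may. What stands is that a patient without a yes/no outcome adds nothing to the likelihood unless imputed, so omission is the natural effect of the default. It remains an inference.

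**Capture is better than a single reading.** There are three recording times, naloxone use is counted, and section 6.3 also has toxicity noted in the dose-escalation program. One missed check need not mean a missing outcome. That lowers the frequency of the problem. The rule nevertheless operates only when an outcome is missing, and classification from the remaining readings is not written down.

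**The reasons for missingness are not documented.** The SAP names none. That a patient is kept off the ward for respiratory depression is plausible from where readings are taken, but it is an assumption, as are the missing rates.

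**Not every lost toxicity raises the dose.** A reader might infer from the table that it does, or that two losses take the choice to 0.20 mg/kg. Going from 2/19 to 1/18 changes the choice under plug-in only, and the SAP does not specify plug-in. The states are also illustrative, with all patients at one dose and only toxic patients missing.

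**Counting every unknown as toxic is not free.** This stands: 40% against 59% correct selection when the highest dose is the true MTD is a substantial loss. Counting death, intensive care transfer, respiratory support or naloxone as toxicity would also redefine the endpoint of section 6.2, which a missing-data rule should not do.

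**Conclusion.** The concern holds as a defect in a stated rule. Section 7.6 makes ignorable missingness the default for a safety outcome, relies on a test that cannot check the mechanism that matters, adds a condition that cannot be evaluated, and gives no action on rejection.

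The direction, if toxic patients are the ones missing, is towards a higher dose. One lost event can move the choice by one level, or early on from lowest to highest. Both switches hold for plug-in and posterior mean under an assumed power model. The trial-level figures (37% against 20% selecting above the MTD) rest on assumed missing rates and on omission. They show what could happen and are not a forecast. With no missing data expected, the problem may never arise. The rule should still be corrected, because it matters only when that expectation fails.

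**What to change.** In section 7.6:

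1. Delete Little's test, and the judgement about type I error, as the basis for handling the primary outcome.
2. Classify a patient with a missed reading from the remaining readings and charted observations, under the existing section 6.2 definition, and record why the reading was missed.
3. For outcomes still unknown, do not assume missingness completely at random. Report the MTD once with these patients omitted and once with all of them counted as toxic, and state whether it changes.
4. Fix in advance how an unknown outcome enters the sequential dose assignment. This choice is for the sponsor, and it should leave the endpoint definition as it is.

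The cost is SAP wording, a little more analysis work, and the possibility of having to report that the MTD is sensitive to the missing outcomes.

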### Time plan for final analyses and evaluation of effect measures

7.7

The statistical analysis will be conducted after the inclusion of the last patient and the publishing of this statistical analysis plan. The assessment of the effect measures will be conducted after the analyses have been performed.

### Statistical software

7.8

The CRM will be conducted in R version 4.2.1 with the integrated development environment using the bcrm package [23] and the jags gibbs sampler. The rest of the analysis will be conducted in STATA ver. 17.

## Discussion

8

The results of this study will provide important evidence on the analgesic safety measures of methadone during hip surgery. The maximal tolerable dose will be used in a future randomized clinical trial. This knowledge is essential when aiming to improve the treatment of hip-fracture patients. The study will run in a real-life setting to increase the feasibility of implementing the methods afterwards. This pre-defined SAP is essential to increase the study's transparency and explicitly describe protocol deviations to increase reproducibility and avoid any risk of reporting bias or data-driven analysis.

## Trial status

SAP version 1.0 was developed on the 15th of November 2022. Protocol to Ethics committee was updated on the 25th August 2022. Recruitment starts January 2023. Recruitment is estimated to be completed in June 2023.

## Availability of data and materials

Due to Danish laws on personal data, data cannot be shared publicly. The person responsible for the research is the principal investigator and corresponding author that together with the Department of Health Research and the University Hospital of Southern Denmark owns the data and has access to the final data-set. To request this data, please contact the corresponding author for more information. For ancillary studies, a new consent will need to be given by the Regional Committees on Health Research Ethics for Southern Denmark.

## Ethics approval

The project was approved by the National Committees on Health Research Ethics.

(S-20200133), registered by the Danish Data Protection Agency (22/29,376), by ClinicalTrials.gov (NCT05581901) and by the Danish Medicine Agency (2022063317).

## Consent to participate

Written informed consent will be obtained from the participants before participation in the study.

## Consent for publication

Not applicable.

## Data Availability

No data was used for the research described in the article.
